### Randomisation and sample size

Block randomisation of size four, performed via a randomisation command in the LifeGuide platform,^36^ will be used to sequentially randomise eligible consecutive consenting participants to one of four groups: (1) 10-session attentional modification group (10AMG); (2) 10-session placebo training group (10PTG); (3) 18-session attentional modification group (18AMG); or (4) 18-session placebo training group (18PTG). This blocked randomisation will be performed separately for those aged 16–24 and those aged 25–60. An allocation concealment mechanism will be used to ensure neither participants nor researchers know the study group to which the next participant will be assigned. This will be automatically performed within the LifeGuide platform (see The intervention section), with participants provided access to appropriate AMG or PTG sessions. Participants randomised to either 10-session condition will receive ten 35 min online sessions across a 4-week period, while those randomised to either 18-session condition will receive eighteen 35 min online sessions across an 8-week period. All online sessions will be administered twice a week on a separate set of days (Monday–Thursday, Tuesday–Friday). Participants randomised to either AMG condition will receive attentional training via the modified training version of the probe-classification visual-probe task, while those randomised to either PTG condition will receive placebo training via the standard version of the probe-classification visual-probe task. To maintain the overall quality and legitimacy of the intervention, code breaks (ie, unblinding) will only occur in exceptional circumstances. Adherence will be monitored electronically via LifeGuide.

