Our previous lab-based, proof-of-concept ABM intervention found reductions in pain intensity and pain interference from pre-ABM to post-ABM were associated with large effect sizes,^27^ although differences in methodology including delivery (online vs lab-based) and number of sessions warrant a more conservative estimate. On this basis, the study will recruit a minimum of 100 with 1:1:1:1 randomisation. This study is powered primarily to establish treatment efficacy for the primary outcome variable of pain interference by considering baseline and measures after session 10 between those randomised to an attentional modification arm and those randomised to a placebo arm. Randomisation should ensure baseline comparability on measures between these two groups, and a difference in beneficial outcomes between these groups will be modelled using a linear mixed model. For an assumed correlation of 0.7 between baseline and end of session 10 measures, a total of 40 per group (ie, 20 per randomised arm) would be needed to detect small to moderate standardised intervention differences (Cohen’s *d*=0.25) with at least 80% power (alpha=0.05, two-sided). The recruitment strategy includes a 20% oversampling to mitigate a loss of power from loss to follow-up.

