### Analyses of the RCT data

#### Quantitative analyses

A full and detailed statistical analysis plan will be written prior to trial closure. In brief, the data analysis will be performed on an intention-to-treat (ITT) basis to provide an unbiased estimate of the treatment effect.^56^ Per-protocol analyses will also be performed (comprising those correctly randomised, without protocol violations, and providing complete data on the primary outcome measure). Sweetman and Doig^57^ have identified five types of protocol violations, namely violations in (1) enrolment (ie, failure to correctly apply eligibility criteria resulting in the enrolment of an inappropriate participant); (2) randomisation (ie, violation of intended randomisation sequence); (3) study intervention (ie, dosing, timing or delivery errors attributable to members of the research team); (4) patient compliance (ie, participants failing to comply with the trial protocol or other requirements of participation in the trial, such as skipping scheduled appointments or sessions); and (5) data collection (ie, a failure by the research team to comply with prespecific trial guidelines for data collection and/or outcome evaluation due to avoidable reasons). Any such violations will be clearly reported.

Analyses undertaken will include the following:

The primary analysis on pain interference will use the initial 2×2×2 structure comprising stage (baseline, 10 weeks), randomised treatment (attentional bias modification training (ABMT), placebo) and randomised number of sessions (10, 18). This comparison will be extended to compare 10AMG and 10PTG after 10 sessions, and to compare 18AMG and 18PTG after 10 sessions.An analysis of pain interference will use the 2×2×3 structure comprising randomised treatment (ABMT, placebo), randomised number of sessions (10, 18) and stage (baseline, endline, follow-up).An assessment of change in pain interference, both within and between groups, for 18AMG and 18PTG, between the end of session 10 and endline.The four randomised arms compared against one another on pain interference at each of baseline, after session 10, endline and follow-up.An age (16–24, 25–60) subgroup analysis using an age subgroup by treatment effect interaction. These analyses will be an extension of (1), (2) and (3) to incorporate age as a subgroup factor.

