The same analyses would apply to the secondary outcome measures. The data will be represented descriptively and graphically by arm, and by treatment and age, and standardised effect sizes reported.

Linear mixed model with random intercepts will be used to analyse the data with, as appropriate, treatment (ABMT, placebo), number of sessions (10, 18) and assessment stage as fixed factors. This approach avoids listwise deletion which would apply in a repeated measures analysis of variance approach. The linear mixed modelling approach uses all of the available data and adheres to ITT. As a secondary analysis we will used multiple imputation chained equations to impute outcome data^58 59^ and use these imputed data sets in the linear mixed model. Pairwise comparisons will follow the same procedure. An assessment of the sensitivity of findings to missing data mechanisms will be undertaken.^60 61^ Specifically, we will use the strategy discussed by Morris and colleagues^61^ whereby multiply imputed values are altered by a randomised group-dependent value prior to analysis. We will run this sensitivity analysis over a factorial arrangement of group-dependent values constraining any altered imputed values to be in the valid response range. The instance of the group-dependent values both being equal to zero will correspond to multiple imputation under missing at random (MAR), and non-zero values would reflect deviations away from this assumption. The analysis plan would apply to the primary outcome measure and secondary outcome measures.

Similar to previous studies,^25 27^ the Reliable Change Index^62^ will be used to assess primary and secondary outcome measures for clinically significant changes. Here, a clinically significant result is a post-treatment score falling outside 2 SD of the mean population of interest (in this study, 2 SD outside pretreatment means). In contrast to tests of statistical significance comparing group means, tests of clinical significance explore effects of treatment on the individual.^63^

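### Randomisation is stratified by age, but the stated main models omit the age stratum; if age predicts change in pain interference, the primary standard error is slightly too large (conservative, minor)

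*Protocol article*

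**What the plan says.** Under Randomisation and sample size, the article specifies "Block randomisation of size four, performed via a randomisation command in the LifeGuide platform" and adds: "This blocked randomisation will be performed separately for those aged 16–24 and those aged 25–60". Age group is therefore a stratification factor, with one participant per arm in each complete block.

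Under Quantitative analyses, the first listed analysis reads: "The primary analysis on pain interference will use the initial 2×2×2 structure comprising stage (baseline, 10 weeks), randomised treatment", with number of sessions as the third factor. The type of model is given next: "Linear mixed model with random intercepts will be used to analyse the data". Its fixed part, which the article qualifies as applying where suitable, is named as "treatment (ABMT, placebo), number of sessions (10, 18) and assessment stage as fixed factors". Age is not in either list. It appears in the fifth analysis, on the age-by-treatment interaction: "These analyses will be an extension of (1), (2) and (3) to incorporate age as a subgroup factor". On that wording, analyses (1) to (3), including the primary one, do not contain age.

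The same section calls itself a brief account and announces a full statistical analysis plan, which is not shown.

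**The concern.** Stratified blocking makes the arms nearly balanced on age group, so the true sampling variance of the treatment contrast excludes the between-stratum component. A model without the stratum still counts that component as residual error. Where the stratum predicts the quantity being compared, the model-based standard error then exceeds the true one: the test rejects less often than its nominal level, and precision already bought by the design is not used.

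The primary comparison is the treatment difference in change from baseline to session 10. What matters for it is whether age group predicts change, not whether it predicts level. At stake is a small amount of power for the primary outcome, and some precision in the comparisons of arms at single time points.

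**Working it through.** **Inputs from the article** (Randomisation and sample size): correlation 0.7 between baseline and session 10; 40 per treatment group, 80 in total; Cohen's d = 0.25; two-sided alpha 0.05; at least 80% power; 20% allowance for loss; "the study will recruit a minimum of 100 with 1:1:1:1 randomisation".

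**Assumed, because the article gives neither:** g, the stratum difference in mean change (in outcome SDs), 0.3 to 0.5; p, the share aged 16–24, 0.3 to 0.5.

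**1. The plan's own sample size.** The figure of 40 per group is reproduced by the repeated-measures within-between interaction with f = d/2 = 0.125. The noncentrality is N·f²·2/(1 − 0.7) = 80 × 0.015625 × 2/0.3 = 8.33, giving power 0.814 at N = 80 (78 would suffice). Recruitment is 80/(1 − 0.20) = 100.

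This calculation corresponds to a treatment difference in change of 0.50 SD: 0.50²/0.03 = 8.33, where 0.03 is the squared standard error from step 2. Power is therefore evaluated at 0.50 SD below, not at 0.25.

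**2. Standard error with the stratum modelled.** Within a stratum the variance of change is 2(1 − 0.7) = 0.60, in squared outcome SDs. SE = √(0.60 × 2/40) = √0.03 = 0.173.

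**3. Standard error without the stratum.** The residual variance of change becomes 0.60 + g²p(1 − p). The estimator's true standard error stays at 0.173 because blocking balances the strata; only the reported one grows, by k = √(1 + g²p(1 − p)/0.60). By normal approximation, type I error = 2[1 − Φ(1.96k)], and power at 0.50 SD = Φ(0.50/0.173 − 1.96k). With the stratum modelled (k = 1), power is 0.823.

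| g | p | residual variance | k | type I error | power at 0.50 SD |
|---|---|---|---|---|---|
| 0.3 | 0.3 | 0.6189 | 1.016 | 0.0465 | 0.815 |
| 0.3 | 0.5 | 0.6225 | 1.019 | 0.0459 | 0.813 |
| 0.5 | 0.3 | 0.6525 | 1.043 | 0.0410 | 0.800 |
| 0.5 | 0.5 | 0.6625 | 1.051 | 0.0394 | 0.796 |

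The loss is 0.8 to 2.7 points. If d = 0.25 is instead taken as the difference in change, the same formula gives 0.303 with the stratum and 0.292 to 0.269 without, a loss of 1.1 to 3.4 points.

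**4. Simulation of the stratified block design** (N = 80, half in each stratum, complete data, 6,000 runs per scenario; power at 0.50 SD):

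| age effect | SE without / with age terms | type I error without / with | power without / with |
|---|---|---|---|
| main effect 0.5 SD | 0.173 / 0.173 | 0.050 / 0.050 | 0.81 / 0.81 |
| main effect 1.0 SD | 0.173 / 0.173 | 0.049 / 0.049 | 0.81 / 0.81 |
| age × stage 0.25 SD | 0.175 / 0.173 | 0.047 / 0.051 | 0.81 / 0.82 |
| age × stage 0.5 SD | 0.182 / 0.173 | 0.037 / 0.048 | 0.79 / 0.82 |
| age × stage 1.0 SD | 0.207 / 0.173 | 0.017 / 0.048 | 0.69 / 0.81 |

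The 0.5 SD interaction row agrees with step 3. The 1.0 SD row shows the direction at an extreme and is not a plausible case. The main-effect rows show that a difference in level cancels from the within-person contrast. A direct mixed-model fit to one simulated data set with a 1 SD age main effect agrees: the treatment × stage standard error is 0.1882 both with and without age as a main effect.

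**5. Single-time-point comparisons, as in analysis (4).** Level differences do not cancel here. For a post-only treatment contrast with a 0.5 SD age main effect, the simulated standard error is 0.230 without age and 0.223 with it, about 3% larger (formula: √(1 + 0.25 × 0.25) = 1.031). The type I error is 0.042 against 0.048, so this too is conservative.

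**The case against.** The strongest reply is that the article is a summary, that covariate lists belong in the announced analysis plan, and that the fixed-factor list carries a qualifier leaving room for more. Part of this stands: the analysis plan can add the terms, which keeps the point minor. But the article does more than stay silent. It fixes the primary structure and names the factors, and the qualifier reads most naturally as choosing among those three for different analyses. Analysis (5) brings age in as an addition to (1) to (3), which confirms that they lack it.

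A second reply is that the effect is conditional and small. This stands in full. The Introduction itself reports only limited evidence that age moderates bias change or symptoms, so a large age × stage effect should not be presumed.

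A third reply is that age is already modelled in analysis (5). That is true, but it is a subgroup analysis with an age × treatment interaction and does not supply the primary estimate.

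A reader might also infer that omitting age undermines the missing-at-random assumption. The documents do not support this. The article does not list the imputation variables, so age cannot be said to be excluded, and it gives no dropout rates by age. It also plans sensitivity analyses for departures from missing at random.

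**Conclusion.** The point holds as a minor one. The stated main models omit a factor used to stratify randomisation. If age stratum predicts change in pain interference, the primary standard error is overstated by about 2–5% and about 1–3 points of power are lost. These figures rest on an assumed 0.3–0.5 SD stratum difference in change, 30–50% aged 16–24, complete data on 80 participants, and a 0.50 SD treatment difference in change.

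Two stronger readings are tempting. One is that the primary standard error is wrong simply because the stratum is left out. It is not: with complete data, an age main effect of even 1 SD leaves it unchanged, and only a relation of age to change matters. The other is that the primary test is invalid. It is not: the error is conservative, randomisation protects the estimate from bias, and the false-positive rate is not inflated.

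**What to change.** In the analysis plan, before unblinding, add age stratum and age stratum × stage as fixed effects in the main models for the primary and secondary outcomes. The interaction term is the one that helps the primary contrast; the main effect helps the single-time-point comparisons in analysis (4). State that age stratum is in the imputation model. Keep age × treatment for analysis (5) only.

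The cost is a line or two of text and two degrees of freedom in the two-stage primary model (three in the three-stage model). No change to recruitment, randomisation or data collection is needed, since age group is known at randomisation.

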**Trial registration number:**

NCT02232100; Pre-results.

Strengths and limitations of this studyThis protocol describes an internet-delivered intervention to explore the efficacy of attentional bias modification training in patients with chronic musculoskeletal pain.The study will recruit a diverse sample of participants in terms of age, socioeconomic status and geographical region.Results will provide important information regarding dose effects, age effects, and participants’ experiences and attitudes using the online intervention.There is limited control over the conditions under which training is completed.Independently verifying participant diagnosis is impossible.

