### Visual-probe tasks

The flow of visual-probe sessions is illustrated in figure 2. In total there will be eight linguistic and eight pictorial probe-classification visual-probe training tasks used in the study, each with different stimuli. A complete description of the stimuli including ratings of valence, arousal, pain intensity, written frequency and low-level features is provided in online supplementary material 1. To briefly summarise, each linguistic visual-probe task includes 32 threatening/neutral and 16 neutral/neutral word pairs. Each task includes eight threatening words from each of the following categories: sensory pain, affective pain, health threat and general threat. Each pictorial task includes 32 threatening/neutral and 16 neutral/neutral image pairs. Each task includes eight threatening images from the following categories: musculoskeletal pain, facial expressions of pain, health threat and general threat. A total of 384 trials are included in each task, with each stimuli pair presented four times for 500 ms and four times for 1250 ms. Within each exposure duration, each stimulus appears twice in the upper location of the screen and twice in the lower location.

10.1136/bmjopen-2019-030607.supp1Supplementary data

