A separate linguistic visual-probe task will be used in the three assessment sessions, featuring different stimuli to the linguistic training visual-probe tasks. The use of separate assessment and training stimuli is necessary to establish whether training effects generalise to novel stimuli not used in the actual training. The same assessment stimuli will be used in all assessment sessions. The ABM training version of the visual-probe task to be completed by AMG groups includes three main stages per trial (figure 1). Following a 500 ms initial fixation point, a stimulus pair is presented in distinct locations (eg, above and below the initial fixation point) for either 500 or 1250 ms. The stimulus pair may be either words or images, although critically includes one threat-related and one neutral stimulus. Stimuli presentation times of 500 and 1250 ms are used as these are the most common stimuli presentation times adopted in chronic pain visual-probe studies (eg, refs 18 20 47) and will allow us to closely compare our results with those of previous research. Immediately following their presentation, the stimuli disappear and a probe appears (either *‘p’* or *‘q’*) in the location of the neutral stimulus. Participants use corresponding keys on their keyboard to indicate the probe letter as quickly and as accurately as possible. In the standard version of this paradigm completed by PTG groups and used in the assessment sessions, the probe replaces the neutral and threat-related stimulus an equal number of times. The probe-classification version of the visual-prove task is argued to encourage a more even monitoring of the display than the probe-position version (ie, which requires participants to indicate the location of a dot, either left/right or up/down), as for the latter participants can adopt biased monitoring strategies favouring one particular region over the other.^48^ As any such biases in monitoring may affect training, we will use the probe-classification version of the visual-probe task.

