For visual-probe data, and as per previous research,^19 27^ practice and incorrect trials will be removed prior to analyses. Box and whisker plots for overall data will be used to reveal overall outliers, which will be removed. Following this, mean response times will be computed for each participant, with any response >3 SD from their individual mean also removed as outliers. This process ensures extremely quick or slow responses do not unduly bias the results, which are typically removed when cleaning and screening visual-probe data in pain-related research (eg, refs 18 64–67). An attentional bias index will then be computed for each stimulus and presentation time condition using the following equation: (TuPl−TlPl)+(TlPu−TuPu)/2. Here T is the threatening stimulus, P is the probe, u is the upper position and l is the lower position. The attention capturing quality of threatening stimuli is measured by subtracting the mean probe classification time for congruent trials from the mean probe classification time of incongruent trials.^21^

Split-half reliability will be computed via a bootstrap procedure, by randomly splitting the total number of trials in two halves, such that each half has the same number of congruent and incongruent trials. Attentional bias scores will be computed for each half and the correlation between them calculated across participants. This procedure will be repeated 100 times, and an average split-half correlation computed.

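### Visual-probe cleaning works trial by trial only, so a session at or near chance accuracy still receives an attentional bias score (minor; mechanism measure only)

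*Protocol article*

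**What the plan says.** The Quantitative analyses section sets out the visual-probe cleaning in order. First, "practice and incorrect trials will be removed prior to analyses". Second, "Box and whisker plots for overall data will be used to reveal overall outliers, which will be removed". Third, individual mean response times are computed, "with any response >3 SD from their individual mean also removed as outliers". The bias index is then calculated. The stated purpose concerns speed: "This process ensures extremely quick or slow responses do not unduly bias the results".

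Under Visual-probe tasks, the probe is one of two letters, and "Participants use corresponding keys on their keyboard to indicate the probe letter as quickly and as accurately as possible". On task size, "each linguistic visual-probe task includes 32 threatening/neutral and 16 neutral/neutral word pairs". The number of trials follows from the presentations per pair, with durations in milliseconds: "A total of 384 trials are included in each task, with each stimuli pair presented four times for 500 ms and four times for 1250". These counts describe the training tasks. The separate assessment task, from which bias is measured, is introduced afterwards without its own count. In the assessment version the probe replaces the threat and the neutral stimulus equally often.

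Sessions are taken remotely, and the strengths and limitations list says: "There is limited control over the conditions under which training is completed".

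**The concern.** All three steps act on single trials. With two keys, a guess is correct half the time, so it passes the first step on the same terms as an attended response. The two response-time steps remove guesses only when their speed is unusual. No step uses a session's overall accuracy, which is the quantity that separates a participant doing the task from one pressing keys.

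Guessed trials say nothing about where attention was, so they pull the index towards zero and add noise. The index is the trial's only measure of attention. The Introduction says that earlier studies could not establish how ABM works and asks whether the number of sessions affects attentional bias. Those are the questions a diluted index would answer less well. The planned split-half reliability would also be computed on a sample that includes chance-level sessions.

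**Working it through.** **Inputs from the protocol article.** 32 threat/neutral and 16 neutral/neutral pairs; 4 + 4 presentations per pair; two response keys; the three cleaning steps; index = incongruent minus congruent mean response time.

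**Assumed, because the article gives no figures.** Response-time means and SDs, 97% accuracy when engaged, a true bias of 10 ms, and a 1.5 × IQR fence for the box plot.

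**1. The stated trial count.** (32 + 16) × (4 + 4) = 384, which agrees. Threat trials: 32 × 8 = 256, or 128 per exposure duration and 32 per cell (threat position by probe position).

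**2. Partial guessing.** Let a share g of trials be guessed and the rest be correct. Accuracy is 1 − g/2. Guesses make up (g/2)/(1 − g/2) = g/(2 − g) of the retained trials. The true bias is multiplied by (1 − g)/(1 − g/2).

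| Accuracy | g | Bias multiplied by |
|---|---|---|
| 90% | 0.2 | 0.8/0.9 = 0.89 |
| 75% | 0.5 | 0.5/0.75 = 0.67 |
| 60% | 0.8 | 0.2/0.6 = 0.33 |
| 50% | 1.0 | 0 |

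This ignores the response-time steps.

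**3. How much of a fully random session survives.** About 384 × 0.5 = 192 trials are correct by chance. In simulation (4000 runs per setting, one exposure duration), 49% of trials remain after the incorrect-trial and 3 SD steps, against 96% for an engaged participant. Adding the pooled fence makes retention depend on speed:

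| Mean response time of random presser | Trials kept |
|---|---|
| 600 ms | 48% |
| 400 ms | 45% |
| 300 ms | 22% |
| 250 ms | 10% |
| 200 ms | 4% |

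**4. The score such a session receives.** The simulated mean lies between −0.7 and +1.0 ms, so zero in expectation. The SD of a single score (without the fence) is 18, 28 and 47 ms for response-time SDs of 80, 120 and 200 ms; engaged participants have 13, 19 and 32 ms. The ratio is about 1.4, as expected from halving the trials: with n trials per cell the SD is roughly s/√n, and √(31/16) ≈ 1.4.

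**5. Effect on the comparison of arms.** Assume a baseline bias of 10 ms, ABM bringing it to 0, placebo leaving it at 10, and a share f of sessions random at endline only, equal in both arms. The observed contrast is (1 − f) × (−10) ms, and placebo shows a change of −10f ms.

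| f | ABM minus placebo | Spurious placebo change |
|---|---|---|
| 0 | −10 ms | 0 |
| 5% | −9.5 ms | −0.5 ms |
| 10% | −9.0 ms | −1.0 ms |
| 20% | −8.0 ms | −2.0 ms |

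**6. What an accuracy floor does.** For a random presser over 384 trials, P(at least 215 correct) = 0.0108 and P(at least 216 correct) = 0.0082, so 216 (56.3%) is the one-sided 1% limit. The chance of reaching 60% is 4 × 10⁻⁵, and of reaching 80% is 1.6 × 10⁻³⁴. The chance-level floor is lenient: a session with true accuracy of 60% passes it with probability 0.94.

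**The case against.** The strongest reply is that the article summarises its analyses, promises a full statistical analysis plan before trial closure, and does not call its cleaning steps exhaustive; an accuracy threshold is a typical detail for that plan. This lowers the weight. It does not remove the point, because the article goes further than a summary here: it orders the steps, gives the SD cut-off and the formula, and says the index is computed next. Followed as printed, that rule scores a chance-level session like an attended one.

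Other objections stand in full:

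- A reader might infer that only incorrect trials are dropped and that half of all guesses always survive. Two response-time steps follow, and under the assumed fence they remove most very fast key-pressing.
- A reader might infer that random pressing gives a score that looks like successful training. Zero is only the expected value, and single scores scatter widely. The article trains attention away from threat and nowhere names zero as the target. Someone who guesses from baseline onwards has no expected change.
- A reader might infer a false ABM effect. That would need more disengagement under ABM than under placebo, and the article gives no evidence of it.
- The index is neither the primary outcome nor a listed secondary outcome.
- Disengagement is not unmonitored: an engagement questionnaire follows every visual-probe session, participants confirm readiness beforehand, and compliance violations are to be reported. None of these stops a chance-level session from being scored.

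**Conclusion.** The point holds as a minor one. The stated cleaning contains no session-level accuracy check, so sessions at or near chance in a two-key, unsupervised task enter the bias analysis. Guesses at ordinary speed survive at a rate of 45 to 48% under the assumed response times and fence. The consequence is a noisier index and an ABM versus placebo contrast pulled towards zero in proportion to the share of such sessions: about 10% at f = 10%. A spurious fall in bias within an arm can appear only if baseline bias is positive and disengagement grows after baseline; the 10- versus 18-session comparison would be affected only if disengagement also differed by length of training.

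The share of chance-level sessions in this trial is unknown, so the actual loss cannot be stated. Pain interference and the other questionnaire outcomes do not depend on the index and are unaffected.

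**What to change.** Add one step before the index is computed: set the bias score for an assessment session to missing when its accuracy is not above chance, using the one-sided 1% binomial limit for the assessment task's actual trial count (fewer than 216 correct if it has 384 trials). Apply it blind to arm, fix it before the data are seen, and use it for the split-half reliability sample as well.

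Because this floor leaves partly guessed sessions in, repeat the bias analysis with a stricter floor, for example 80% correct. Because exclusion happens after randomisation, also repeat it with no exclusion. Report accuracy and excluded sessions by arm and stage.

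The cost is a sentence or two of analysis wording and short extra runs. Trial-level accuracy must already be recorded in order to drop incorrect trials, so no new data are needed. The downside is a few missing bias scores.

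### The attentional bias index is printed without its outer bracket, so it contradicts its own verbal definition; coded literally, it weights lower-probe trials 2:1 (minor, wrong as written)

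*Protocol article*

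**What the plan says.** The scoring rule is in the visual-probe paragraph of Quantitative analyses in the protocol article. After trial cleaning, "An attentional bias index will then be computed for each stimulus and presentation time condition", "using the following equation: (TuPl−TlPl)+(TlPu−TuPu)/2". The symbols are then defined: "Here T is the threatening stimulus, P is the probe, u is the upper position and l is the lower position". The next sentence says what the index measures, namely the attention-capturing quality of threat, obtained by "subtracting the mean probe classification time for congruent trials from the mean probe classification time of incongruent trials".

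The scores are used again in the following paragraph, on split-half reliability: "Attentional bias scores will be computed for each half and the correlation between them calculated across participants".

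Two statements under Visual-probe tasks bear on how the probe positions should be weighted. Within each exposure duration, "each stimulus appears twice in the upper location of the screen and twice in the lower location" (this stands in the description of the training tasks). In the standard version, used for the placebo groups and for assessment, "the probe replaces the neutral and threat-related stimulus an equal number of times".

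**The concern.** A division sign after the second pair of brackets applies to that pair only. As printed, the index is therefore the full lower-probe contrast plus half of the upper-probe contrast. The sentence that explains it describes a plain difference of two means, in which both contrasts carry the same weight. An analyst cannot follow both.

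The index scores every assessment of attentional bias: baseline, session 10 in the 18-session arms, endline and six-month follow-up. The introduction notes that earlier trials could not establish how the training works, and it calls it worthwhile to examine whether the number of sessions affects patterns of bias. A literal coding of the formula would raise no warning, because the resulting values look plausible. The article says that the full SAP is still to be written, so the printed expression could be carried into it and into the code.

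**Working it through.** **Inputs.** The printed formula, the symbol definitions and the verbal definition all come from Quantitative analyses. The protocol gives no cell means or variances, so the millisecond values below are illustrative assumptions. There is no stated figure to reproduce.

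**Notation.** Let L = TuPl − TlPl (probe in the lower position) and U = TlPu − TuPu (probe in the upper position). In each, the first cell is incongruent (probe away from threat) and the second is congruent (probe at the threat).

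- Printed, by operator order: L + U/2. Weights 1 and 1/2, a ratio of 2:1.
- Verbal definition: (TuPl + TlPu)/2 − (TlPl + TuPu)/2 = (L + U)/2. Weights 1/2 and 1/2, a ratio of 1:1.

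The second line takes the mean of each pair of cells with equal weight. That fits the balanced presentation described under Visual-probe tasks, which gives no reason for a 2:1 weighting.

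**Scale.** If L = U = b, the printed form gives b + b/2 = 1.5b and the verbal definition gives (b + b)/2 = b. A bias of 10 ms is reported as 15 ms.

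**Illustrative cell means (ms), in the order TuPl, TlPl, TlPu, TuPu:**

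| Case | Cell means | Printed | Bracketed | Verbal |
|---|---|---|---|---|
| Uniform 20 ms bias | 620, 600, 600, 580 | 30 | 20 | 20 |
| 20 ms at lower probe only | 620, 600, 580, 580 | 20 | 10 | 10 |
| 20 ms at upper probe only | 600, 600, 600, 580 | 10 | 10 | 10 |
| No bias, 10 ms slower when threat is upper | 610, 600, 580, 590 | 5 | 0 | 0 |

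The bracketed form matches the verbal definition in every row.

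**Threat-position effect.** Suppose responses are slower by d whenever the threat is in the upper position, with no bias. Then L = d and U = −d. The printed form gives d − d/2 = d/2, and the bracketed form gives (d − d)/2 = 0. The last row of the table is this case with d = 10. The same algebra covers opposite contrasts: L = +20 and U = −20 gives +10 printed and 0 bracketed.

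**Precision.** Assume L and U are independent, each with variance v.

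- Printed: v + v/4 = 1.25v. Dividing by 1.5² = 2.25 to return to the scale of b gives 0.556v.
- Bracketed: (v + v)/4 = 0.500v.
- Ratio: 0.556/0.500 = 1.11, so the variance is about 11% larger and the SD about 5% larger (√1.11 ≈ 1.05). Equivalently, the relative efficiency is 1/1.11 = 0.90.

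**The case against.** The strongest reply is that the intent is not in doubt. The explanatory sentence allows only one reading, and dividing by 2 has no evident purpose other than to average the two contrasts. An outer bracket or a fraction bar may also have been lost in typesetting or text extraction. Both points stand as reasons for treating this as a probable slip of notation. They do not remove it: the text as it reads has no such bracket, nothing elsewhere in the article supplies one, and code follows the expression it is given.

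A reader might infer that every bias score, every test of change in bias and every split-half correlation would be wrong. The protocol does not support that. No scoring code is shown, so it is not known that the literal form would be used. The factor of 1.5 under a uniform bias is a change of units: it leaves test statistics, standardised effects and correlations as they were. Only the unequal weighting can alter them. A threat-position effect that training does not change would have the same expectation in every randomised arm, and so would cancel in comparisons between arms. The case of opposite contrasts at the two probe positions is illustrative; the protocol does not suggest that such a pattern is expected.

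A reader might also infer that the slip defeats the protocol's stated aim of comparability with earlier research. That statement, under Visual-probe tasks, justifies the 500 ms and 1250 ms presentation times and says nothing about how the index is scaled. Scores in milliseconds would still be on a different scale from scores formed by the verbal definition.

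Finally, the index is not the primary outcome or a listed secondary outcome, and none of the listed analyses of pain interference uses it.

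**Conclusion.** The point holds as a minor error, wrong as written: the printed equation and the definition in the same paragraph disagree. If the equation is coded literally:

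- a uniform bias is overstated by a factor of 1.5 in milliseconds;
- lower-probe trials count twice as much as upper-probe trials;
- half of any threat-position effect remains in the score;
- error variance after rescaling is about 11% larger.

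The first figure assumes equal bias at both probe positions. The last assumes equal and independent variances of the two contrasts. The weighting and the leakage of a position effect are algebra and need no distributional assumption.

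The consequence is confined to the attentional bias scores and what is derived from them. It does not reach pain interference, the listed secondary outcomes, the sample size or the efficacy conclusion, so the documents do not support ranking it with errors that do.

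**What to change.** Print the index as [(TuPl−TlPl)+(TlPu−TuPu)]/2 in the protocol and carry that form into the SAP. Check the scoring code against it, for instance by confirming that a uniform 20 ms bias returns 20 and that a pure threat-position effect returns 0. The same function should be used for the split-half scores.

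The cost is one pair of brackets and one code check. The design, the data collection and the planned analyses of the primary and secondary outcomes stay as they are.
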